- Uterine malformations (class U1-U6 according to ESHRE/ESGE-classification) (30)
- Patients with contraindications to surgery
- Patients undergoing ART with donated oocytes

RANDOMIZATION

After verification of eligibility, signed informed written consent participants will be randomly assigned to either undergo first-line ART or first-line surgery, followed by ART by equal allocation, 1:1. The randomization procedure will be stratified for participating center (permuted block design). Randomization will be performed at each site using the web-based instrument Red Cap. All inclusion criteria and no exclusion criteria must be met. One month before first treatment (IVF or surgery), inclusion and exclusion criteria are entered into the randomization/registration application RedCap. Patients withdrawn from the study after randomization but before treatment will be substituted by newly enrolled patients. Patients withdrawn from the study after first treatment will not be substituted. Username and password are required to log in; each investigator authorized to register patients has a personal login username and password. If all criteria are met, patients are registered, and the allocated patient number is recorded in the patients’ medical file.

There could be some uncertainty surrounding participants' willingness to engage in a Randomized Controlled Trial (RCT) comparing two fundamentally distinct approaches. Therefore, we intend to offer women who fulfill eligibility criteria but decline randomization the opportunity to take part in a parallel study – a prospective cohort study, that would provide valuable real-world outcomes of two different approaches to treatment of endometriosis -associated infertility. This parallel study will evaluate identical outcomes to those in the randomized trial. However, instead of random assignment, participation decisions will be made by the patients themselves, resulting in what is commonly referred to as a patient preference trial.

DEFINITION START OF TRIAL

Start of trial will be defined as start of first treatment which will be either surgery or first ART cycle (e.g start of FSH injections).

DEFINITION END OF TRIAL

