**Additional analysis**

– Exploratory subgroup analyses will not be adjusted for multiplicity.

– Safety outcomes will be summarized descriptively by treatment group (frequency, severity, relation to treatment).
– All available data will be used, including outliers.
– Missing outcome data will be handled under the missing-at-random assumption via maximum likelihood in mixed models; for regression models requiring complete covariates, complete-case analysis will be applied.

Covariates

Primary and secondary outcomes will be adjusted for prespecified covariates (age, BMI, AMH, ART type, center), chosen based on clinical relevance and prior evidence.

POWER CALCULATION AND SAMPLE SIZE

The sample size calculation was based on a two-sample comparison of proportions with a two-sided α=0.05 and 80% power. Based on observational data (18, 19), the cumulative live birth rate (CLBR) after three IVF cycles was assumed to be 55% in the ART-only group and 71% in the surgery+ART group (relative risk ≈1.29). This yields a required sample size of 142 participants per arm (284 total). Allowing for 20% attrition, the planned total sample size is 350 participants.

The necessary sample size for this study is estimated to 323 patients to accommodate a statistical analysis method. This estimation uses the 'pwr' package in R, specifically employing the power.prop.test method, which is designed to compare two proportions. This method is more aligned with contemporary statistical practices and provides a clear, transparent methodology for determining the required sample size based on expected success rates.

This means inclusion of 29 patients from/each center/year and 15 surgeries/year. In a Swedish study published in 2022 the prevalence of endometriosis in patients referred for ART-treatment was 21.8% and 17.2% of women had DE (14). In 2021 almost 10 500 IVF cycles were performed in Sweden, while more than 5 500 of those were first-time IVF/ICSI with autologous gametes ((46) Figure 22).

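### The power section prints a second "necessary" total of 323 that contradicts its own 284 evaluable and 350 planned, and that cannot be reproduced from its stated inputs

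*Protocol*

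**What the plan says.** All the figures stand in the protocol under Statistical Considerations, Power Calculation and Sample Size.

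- The first paragraph describes a "two-sample comparison of proportions with a two-sided α=0.05 and 80% power". It assumes a cumulative live birth rate of 55% with ART alone and 71% with surgery before ART, and reports a requirement of 142 per arm, 284 in total. It continues: "Allowing for 20% attrition, the planned total sample size is 350 participants".
- The second paragraph states: "The necessary sample size for this study is estimated to 323 patients to accommodate a statistical analysis method". It names its tool as "specifically employing the power.prop.test method, which is designed to compare two proportions" and recommends the approach as modern and transparent. It gives no event rates, power or attrition of its own. It does not say whether 323 counts enrolled or evaluable patients, and it does not mention 284 or 350.
- The third paragraph begins: "This means inclusion of 29 patients from/each center/year and 15 surgeries/year".

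Elsewhere the total is 350. The synopsis gives it as the planned sample size, and the section on interim analysis sets the single interim look at 175 patients. Randomisation is "followed by ART by equal allocation, 1:1".

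**The concern.** Two consecutive paragraphs present the outcome of the same kind of calculation, a comparison of two independent proportions, and reach different totals with no change of input to explain the difference. The second number is called necessary and comes with a recommendation of its method, so a reader could take it to supersede the first. The accrual sentence comes directly after 323 and is worded as its consequence, although its rate belongs to 350.

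What is at stake is the power claim. The label of necessary on a number below 350 is a loose end in a protocol that itself expresses doubt about patients' willingness to be randomised. If that number were ever cited as sufficient, its meaning would decide whether 80% power is kept, and the protocol does not give that meaning.

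**Working it through.** **Inputs**, all from the protocol: p1 = 0.55, p2 = 0.71, difference 0.16, mean 0.63; two-sided alpha 0.05 (z = 1.96); power 80% (z = 0.8416); 1:1 allocation; 20% attrition; three years of inclusion (synopsis); four surgical centres (Study Treatment, Surgical Procedure).

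**Step 1: reproduce 284.** With the pooled variance under the null:

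n per arm = [1.96·√(2·0.63·0.37) + 0.8416·√(0.55·0.45 + 0.71·0.29)]² / 0.16² = 141.75, so 142 per arm and 284 in total.

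The protocol's own figure is reproduced exactly. Power at 284 evaluable is 80.1%.

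**Step 2: reproduce 350.** 284/0.80 = 355, and 284 × 1.2 = 341. The planned 350 lies between these two conventions. At exactly 20% loss it leaves 350 × 0.80 = 280 evaluable and 79.5% power. It holds 284 evaluable up to a loss of 1 − 284/350 = 18.9%.

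**Step 3: try to reproduce 323** from the same rates.

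| Variant | Total |
|---|---|
| Pooled, 80% power | 284 |
| Arcsine, 80% (141.3 per arm) | 284 |
| Unpooled, 80% (139.01 per arm) | 280 |
| Continuity-corrected, 80% | 308 |
| One-sided, without / with continuity correction | 224 / 248 |
| 284 with 20% attrition, by division / by multiplication | 355 / 341 |

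None gives 323. Inputs that the protocol does not state come close:

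- 85% power gives 323.9 with the pooled formula (162 per arm, 324 after rounding up) and 2 × 161.7 = 323.3 with the arcsine formula.
- About 12% attrition gives 284/0.88 = 322.7.

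**Step 4: what 323 would imply.**

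- As enrolled: 323 × 0.80 = 258.4 evaluable, power 76.2%.
- As evaluable: power 84.9%, and 323/0.80 = 404 to be enrolled, against 350 planned.

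Either way it disagrees with the first paragraph of the section.

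**Step 5: which total does the rest of the protocol use?**

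- Accrual: 29 × 4 centres × 3 years = 348. Conversely 350/12 = 29.2, while 323/12 = 26.9.
- Interim trigger: 175 × 2 = 350.
- Synopsis: 350.

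**The case against.** The strongest reply is that 323 is an orphan. It appears once. The recruitment target, the interim trigger and the accrual rate all follow 350. The DSMB charter judges recruitment against the planned sample size, and 350 is the only number the protocol labels as planned. This stands. A reader might infer from the two totals that the size delivering 80% power is left open. The protocol does not support that: 284 evaluable is stated and reproduces exactly, and 350 is used consistently.

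It is also fair to say that 76% power must not be quoted on its own. It holds only if 323 means enrolled and the 20% attrition from the preceding paragraph applies. On the other reading power is about 85%, and the trouble is instead that 350 would be too few. No passage makes 323 a point at which recruitment closes.

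A reader might further infer that 323 was computed for 85% power or with 12% attrition. Both come close arithmetically, but neither is stated, so neither should be treated as the origin.

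Finally, 284/0.80 = 355 could suggest that 350 is too small. That asks too much. The gap costs half a percentage point of power at exactly 20% loss, and under the multiplicative convention (341) 350 is already enough. The section on randomisation also replaces patients who withdraw before treatment. If 350 is counted after replacement, those withdrawals do not use up the allowance.

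None of this explains 323. It remains a printed requirement that does not follow from the inputs beside it.

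**Conclusion.** The point holds as an error in one stated figure. The protocol calls 323 necessary. Its own rates, alpha, power and attrition give 284 evaluable, and they support 350 randomised to within rounding. No standard variant at the stated 80% power turns those inputs into 323. The conflict remains whether 323 is read as enrolled (about 258 evaluable and 76% power after 20% loss) or as evaluable (about 85% power, about 404 to enrol).

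The reach is limited. The primary analysis, the interim trigger and the recruitment plan do not depend on 323, and the target of 350 is adequate. As a side note, 350 with exactly 20% loss gives 79.5% power rather than 80%, a difference of wording and not a reason to raise the target.

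The figures assume the normal-approximation comparison of two proportions without continuity correction, which is the version that reproduces the protocol's 142 per arm. They also take losses as equal in the two arms. The accrual check assumes that the centres meant are the four surgical centres.

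**What to change.** Delete the 323 figure and keep one chain: 284 evaluable for 80% power, 350 randomised, 29 per centre per year over four centres and three years. If the paragraph is kept to name the software, it should report the 142 per arm that the method returns.

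If 323 was meant to stand, state the power and attrition behind it, say whether it counts enrolled or evaluable patients, and reconcile it with 350 in this section, the synopsis, the interim trigger and the accrual sentence.

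In the same edit, give either the power as about 79.5% at 20% attrition, or the attrition allowance as about 19% at 80% power. No move to 355 is needed.

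If 350 is kept, the cost is a text correction, with no change to recruitment, follow-up or analysis. The stated power or attrition allowance becomes slightly less favourable.

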# INTERIM ANALYSIS AND STOPPING RULES

An independent safety and monitoring board (DSMB) will conduct one interim analysis when 175 patients have been enrolled in the study and completed either their surgery or first IVF treatment, whichever occurs first. Because each participant has a three-year follow-up and recruitment will be completed within three years, only a limited proportion of primary outcomes will be available at the interim analysis. The analysis will therefore primarily address recruitment feasibility, participant safety including comparison of complication rates between study centers.  The DSMB will monitor adverse events in both arms. For surgery, expected complication rates have been described previously in this protocol (9.9% Clavien–Dindo grade 1–2, 3.3% grade ≥3), while ART carries a different spectrum of risks (e.g. ovarian hyperstimulation, infection, or bleeding). A substantially higher-than-expected complication rate in either arm, major discrepancies between centers or other safety concerns may prompt the DSMB to recommend protocol modifications or early termination.

Recommendations from the DSMB will exclusively be communicated to the Trial Steering Committee. Further details regarding the DSMB can be found in the DSMB charter (Appendix).

# ETHICAL CONSIDERATIONS

RISK-BENEFIT CONSIDERATION

By addressing the research questions, we aim to provide evidence to improve patient outcomes in a population that currently faces challenges in fertility treatment due to endometriosis. The research has the potential to benefit participants by improving their chances of successful conception and live birth rates.

Participants in the study may face several direct risks, including physical risks associated with surgery and assisted reproductive technologies, such as infection, or pre- and postoperative complications. Additionally, there may be psychological risks related to the emotional stress of undergoing medical procedures and the uncertainty of treatment outcomes. Furthermore, there are also risks associated with the collection and storage of sensitive medical data, which must be mitigated through robust data protection measures.

In the long term, the research may contribute to improving the understanding and management of endometriosis-related infertility, thereby potentially benefiting future patients.

INSTITUTIONAL REVIEW BOARD/ETHICS COMMITTEE

The study protocol, patient information, and informed consent are approved by Swedish Ethical Review Authority ( dnr: 2024-04293-01, approved 7^th^ October 2024, amendment, dnr: 2025-03699-02, approved 17^th^ June 2025).

Any significant protocol modifications must be submitted to the relevant Independent Ethics Committee or Institutional Review Board for review and approval before implementation. Upon approval from the appropriate committee or board, the investigator will proceed with implementing such protocol modifications. However, in cases of urgent safety concerns, protocol modifications will be promptly implemented without prior approval.

INFORMED CONSENT AND WITHDRAWAL

Before being enrolled in the study, patients will receive both oral and written information on the study objectives, all treatment procedures, and the anticipated and potential adverse events. They will be informed about the strict confidentiality measures regarding their patient data, ensuring that only their treating physician and authorized study personnel will have access to their medical records. Patients will have the freedom to withdraw their consent for study participation at any time, with or without providing a reason, and this decision will not impact their subsequent treatment options or care.

Written informed consent must be obtained from all participants before they are enrolled in the study. The investigator who provided the written and verbal information should also sign the Informed Consent Form during the same encounter. The signed Informed Consent Form should be retained in the Investigator's File, and a copy should be provided to the study participant.

Participants will consent to the following:

- Participation in the study
- Regulatory authorities and the sponsor's representatives (e.g., monitor) gaining full access to hospital records.
- The control and collection of data for the study
- The recording, collection, processing, and storage of data in a database
- Using of data and images for education, lectures, scientific presentations and publications

PATIENT PROTECTION AND GOOD CLINICAL PRACTICE

The responsible investigator will ensure that the study is conducted in accordance with the principles outlined in the Declaration of Helsinki and/or relevant Swedish or National laws and regulations, whichever offers the highest level of protection for the patient. Participants will be clearly informed that the data collected in the study will adhere to the General Data Protection Regulation (GDPR) (EU 2016/679), ensuring that no subject participating in the study will be identifiable. Women participating in the study will receive treatment in alignment with the international guidelines on Good Clinical Practice (GCP) as defined by the European Parliament (EG596/200).

SUBJECT IDENTIFICATION

Participating patients will be assigned a study-specific code, comprising a two to six-digit number. This code will be utilized for patient registration in the study database. The woman's social identification number will not be included in the database. The key to decipher the code will be accessible solely to the investigator.

# GENDER PERSPECTIVE

Endometriosis is a prevalent condition, yet it is rarely acknowledged as a public health concern, despite its pervasive impact across patients' lifecycles. National guidelines were not issued until 2018, and many women with endometriosis report a lack of awareness and understanding of the disease within society (47). Diagnostic delays are documented in some studies, indicating that patients can suffer from symptoms of this disease up to ten years before a diagnosis of endometriosis is made and treatment is started (48).

A Swedish epidemiological study conducted in 2019 revealed that 45% of teenage girls experience frequent school absences due to dysmenorrhea, yet only 7% of these girls were given the advice to seek doctor consultation (49). Subfertility often arises as a consequence of endometriosis. In another Swedish study involving women seeking assistance for fertility issues, 75.8% of patients were unaware of their endometriosis diagnosis upon initial consultation at the reproductive medicine center (3). This suggests that society commonly perceives menstrual pain as a normal discomfort that women are expected to endure.

# SIGNIFICANCE OF STUDY

Clinical significance

Endometriosis is a prevalent disease among women with infertility, with negative impact on psychological and physical well-being. The management of infertility in women with severe endometriosis is a subject of ongoing debate, with a lack of robust evidence for optimal treatment strategies. Both surgery and ART-treatments in this population may lead to serious complications and are associated with significant costs to society. To date, there are no results from RCTs evaluating potential benefits of endometriosis surgery prior to ART on subsequent reproductive outcomes. This study has the potential to significantly impact the clinical approach to infertility treatment in women with advance endometriosis. Despite the challenges and the coordinated effort required for this RCT, the results promise to be valuable for the scientific and clinical communities.

Implementation

Endometriosis is a very prevalent condition (22 % of infertile women) and this research project will indeed affect many patients, regardless of the results.

The research group is presently drafting national guidelines for the treatment of infertility in patients with advanced endometriosis. The findings of this study will be integrated into these guidelines to assist decision-making for women with severe endometriosis and infertility.

Additionally, in a consensus document from the European Society of Human Reproduction and Embryology (ESHRE) on endometriosis, it is noted that there is a dearth of randomized controlled trials regarding surgery prior to assisted reproductive technology.

The results of the study will most probably affect guidelines and care for women with severe endometriosis and infertility. It will possibly also lead to insights how to treat women with less severe endometriosis. Other aspects, such as centralization of advanced surgery as a concept will also be tested.

# ADMINISTRATIVE CONSIDERATIONS

FINANCING

This academic study is sponsored by Region Stockholm and Karolinska Institutet, Forte, Västra Götaland Region and the Swedish Medical Society.

The Obstetric and Gynecological department at Södersjukhuset, Stockholm, will serve as the coordinating entity for the study. All central administrative expenses associated with the trial, including statistics, monitoring, and questionnaires, are funded through research grants. The aim is to secure adequate grants to cover, either partially or fully, the study-specific costs for each participating site. Each participating center is at liberty to seek financing independently.

PUBLICATION POLICY

Prior to publication of the main fertility outcome, no other publications concerning fertility outcomes on segments of the cohort may be pursued. The Coordinating Investigator and principal investigator Stockholm ([name] and [name]) will serve as first and last authors of the primary outcome and fertility outcome publication. Additionally, members of the Trial Steering Committee must be listed as (co)-authors in all other publications. Each member of the sub-committees will be listed as authors for their respective sub-objectives. The chair of each sub-committee will be either the first or last author and will compile the initial manuscript draft.

The Coordinating Investigator and principal investigator Stockholm will contribute to the data interpretation and determine the authorship order for each publication from the sub-committees. One author (principal investigator) from each participating site, contingent upon data completeness and quality, will be listed as a co-author on any publication reporting the main findings of the Endo-SOFT trial, including reports on fertility outcomes and other significant publications. In cases where the number of authors is restricted by the scientific journal, contributing sites with the highest participant recruitment and completed follow-up will be selected.

All investigators must agree that, upon completion of data collection and analysis by the study statistician, if they do not concur with the outcome results, they reserve the right to abstain from authorship of the manuscript. However, the data collected from their site will be retained and analyzed as agreed upon at the study's inception, consistent with this agreement.

Sub-analysis other than primary and secondary outcomes from the Endo-SOFT trial

Additional sub-analyses or research projects beyond the primary and secondary outcomes outlined in the Endo-SOFT trial are permitted and encouraged. However, permission must be sought from the Trial Steering Committee through a written application. This application must include details such as the primary and secondary objectives, inclusion and exclusion criteria, the name of the individual responsible for manuscript preparation (including the first and last author), the intended journal for submission, and approval from the respective institutional review board. The final decision regarding authorship will be made by the Trial Steering Committee.

ADHERENCE TO PROTOCOL AND PROTOCOL AMENDMENT

Adherence to the study protocol is imperative, and any deviations must be meticulously documented. The Trial Steering Committee must be promptly notified of any such deviations. Changes or additions to the study protocol can only be deliberated upon and authorized by the coordinating investigator, study coordinator, trial steering committee, and statistician. Following approval by the appropriate Independent Ethics Committee or Institutional Review Board, the investigator is responsible for implementing these protocol modifications. However, in cases of urgent safety concerns, protocol modifications shall be implemented immediately.

